#### Reimbursement

The project will provide the following support to participating practices:

1. Intervention and control practices: Reimbursement for the practice nurse attendance at the COPD diagnosis and spirometry workshop (AUD270); payment for the practice nurse to undertake the medical record search (AUD500); reimbursement for practice nurse time for case-finding consultations (AUD38.50 for each appointment, for up to 60 patients per practice); continuing professional development points for workshop attendance.

2. Intervention group: reimbursement for practice nurse attendance at the COPD team management workshop (AUD270); reimbursement for GP attendance at the team management workshop (AUD450); category two continuing professional development points for GPs.

Once a diagnosis of COPD is made, any medical or practice nurse consultations that are required for clinical management may be funded through normal practice processes.

Small gifts (food baskets) will be provided to practice reception staff as thanks for their assistance in making follow-up telephone calls.

#### Data analysis

Data collation will be managed using Access, and data analysis undertaken using the Statistical Package for the Social Sciences (SPSS) by a statistician blind to group allocation. Analysis will be by intention to treat, i.e., by the diagnosis assigned by the practice nurse/GP on the basis of case-finding spirometry, including patients whose diagnosis of COPD is not confirmed by the project officer. Intra-cluster (practice) correlation coefficients will be determined and published for all primary outcome variables to assist future research.

The effect of the intervention on outcomes measured on a continuous scale (such as SGRQ score) will be estimated and tested using mixed model analysis of variance in which time and treatment group will be fixed effects and GP practice and subject nested within practice will be random effects. The effect of the intervention on the dichotomous variables (such as smoking and vaccination status) will be analysed using generalised estimating equations with a logistic link and a model structure that is analogous to that described above.

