**Design:**

A pragmatic cluster randomised trial will test the hypothesis that intervention by a practice nurse-general practitioner (GP) team leads to improved health-related quality of life and greater adherence with clinical practice guidelines for patients with newly-diagnosed COPD, compared with usual care. Forty general practices in greater metropolitan Sydney Australia will be recruited to identify patients at risk of COPD and invite them to attend a case finding appointment. Practices will be randomised to deliver either practice nurse-GP partnership care, or usual care, to patients newly-diagnosed with COPD.

The active intervention will involve the practice nurse and GP working in partnership with the patient in developing and implementing a care plan involving (as appropriate), smoking cessation, immunisation, pulmonary rehabilitation, medication review, assessment and correction of inhaler technique, nutritional advice, management of psycho-social issues, patient education, and management of co-morbidities.

The primary outcome measure is health-related quality of life, assessed with the St George’s Respiratory Questionnaire 12 months after diagnosis. Secondary outcome measures include validated disease-specific and general health related quality of life measures, smoking and immunisation status, medications, inhaler technique, and lung function. Outcomes will be assessed by project officers blinded to patients’ randomization groups.

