### Outcome measures

#### Data collection—patients

Once the project officer has received the consent form, contact details, and spirometry worksheet for a patient, they will arrange a visit as soon as possible for baseline assessment, either at the patient’s home or at the GP’s practice according to patient preference. The project officer will collect demographic data including age, gender, body mass index, employment status, education, and country of birth, and data for outcome and process measures. Further data collection will occur at 6 months (by telephone and mail) and 12 months (face to face).

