#### Outcome measures—patients

The primary outcome measure will be disease-specific quality of life assessed by the St George’s Respiratory Questionnaire (SGRQ [52]). Secondary outcome measures include: patient awareness of COPD diagnosis, COPD Assessment Test (CAT, a disease specific QOL measure [53]); smoking status by self-report and from carbon monoxide analysis (Smokerlyzer, Bedfont Scientific Ltd, Maidstone, UK) and readiness to quit if applicable; immunisation rates; medication including appropriate inhaler prescription and effective inhaler use; referral for pulmonary rehabilitation or referral for or provision of exercise prescriptions; disease related knowledge [54]; patient satisfaction; healthcare utilisation; and lung function. The relationship between objectives, outcomes, measures, and hypothesis is outlined in Table 1.

**Table 1 T1:** Relationships between objectives, outcomes, measures and hypotheses

**Objective**	**Hypothesis**	**Outcome**	**Measure**	**Visit**
To assess the effectiveness of early intervention by a GP-practice nurse partnership, in patients newly identified as having COPD	Early intervention by a GP–practice nurse partnership will improve outcomes for patients with COPD, compared with usual care	Improvement in disease related quality of life	St George’s Respiratory Questionnaire (SGRQ) [52]	1,2,3
			COPD Assessment Test (CAT)	1,2,3
		Improved smoking cessation rates	Participation in smoking cessation program; quit rates (self-report)	1,2,3
			Validation of smoking cessation (where applicable) by carbon monoxide analysis	1,3
		Improved compliance with COPD immunisation recommendations	Influenza and pneumococcal vaccination status (self-reported)	1,3
		Improved prescribing and use of medications for COPD	Audit of prescribing against COPD-X guidelines	1,2,3
			Inhaler technique score using published checklists [43]	1,3
		Increased referral for pulmonary rehabilitation	Completion of pulmonary rehabilitation (self-reported)	1,2,3
		Increase in disease related knowledge	COPD knowledge questionnaire score [54]	1,3
		Improved general health status	General health status question (using preliminary question from SGRQ) [52].	1,2,3
		Slower decline in lung function	Post-bronchodilator FEV_1_	1,3
To assess the acceptability and feasibility of team-based vs conventional management of patients with COPD		Improved team-work between GP and practice nurse	Collaborative Practice Scale, VAS scale for team management of COPD	End of study

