#### Sample size calculations

The sample size calculation is based on a minimum clinically important difference for the primary outcome measure (SGRQ) of 4.0 [52], between subject standard deviation in SGRQ of 13 in a similar population [54], intra-cluster correlation coefficient of 0.01, and a resultant design effect of 1.09 for a cluster size of 10. With this design effect, a sample size of 200 patients completing each arm will provide >80% power to detect a difference of 4 or greater in SGRQ (calculations in PASS software). Forty practices will each invite 300 patients to attend a case-finding appointment, and within each practice this is expected to produce 12 patients with a new diagnosis of COPD; loss to follow-up of 20% by 12 months has been assumed. The projected recruitment rate is derived from the response rate to invitation (25%), and the yield of new diagnoses (21%) in our recently completed case-finding project [10].

This sample size will also confer 90% power to identify a doubling of the expected rate of correct inhaler use (from 20% to 40%) at a significance level of 5% (based on an ICCC of 0.1, and design effect of 2.1).

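### As stated, the SGRQ model tests an arm difference averaged over visits, not the 12-month difference that is the primary outcome and the basis of the sample size

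*Protocol article*

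**What the plan says.** - **Outcome.** The abstract (Design) sets the primary outcome as health-related quality of life on the St George's "Respiratory Questionnaire 12 months after diagnosis".
- **Visits.** Table 1 lists SGRQ at visits 1, 2 and 3. From Data collection—patients, visit 1 is the baseline ("they will arrange a visit as soon as possible for baseline assessment"); the others are at 6 and 12 months.
- **Sample size.** It rests on a "minimum clinically important difference for the primary outcome measure (SGRQ) of 4.0" and states that "a sample size of 200 patients completing each arm will provide >80% power to detect a difference of 4 or greater in SGRQ". Loss to follow-up is counted to 12 months.
- **Analysis.** "The effect of the intervention on outcomes measured on a continuous scale (such as SGRQ score) will be estimated and tested" in a "mixed model analysis of variance in which time and treatment group will be fixed effects and GP practice and subject nested within practice" as random effects. Dichotomous outcomes get generalised estimating equations of analogous structure.

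The Data analysis section mentions no arm-by-time interaction, no contrast at 12 months and no baseline covariate. It does not say whether the baseline score is one of the responses.

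**The concern.** A model whose fixed effects are time and treatment group has a single treatment coefficient, common to all visits in the response. If baseline is one of them, that coefficient averages in a visit at which the intervention cannot yet have acted. The primary test would then target a smaller quantity than the one the abstract defines and the sample size is built on, and the trial could miss the effect it was sized to find. The reported estimate would also understate the 12-month benefit, so it could not be read against the 4-point minimum important difference. The same structure carries over to the other continuous outcomes and, by analogy, to the dichotomous ones.

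**Working it through.** **Inputs from the protocol** (Sample size calculations): difference 4, SD 13 (variance 169), ICC 0.01, 10 patients per practice, 200 completers per arm, hence 20 practices per arm.

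**Assumed, not in the protocol:** two-sided 5% for SGRQ (5% is stated only for the inhaler-use calculation); within-patient correlation ρ of 0.5 to 0.8; the 6-month difference d6.

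**1. The plan's own figure.** Design effect = 1 + 9 × 0.01 = 1.09. Effective n = 200/1.09 = 183.5 per arm. SE = 13 × √(2/183.5) = 1.357. Power = Φ(4/1.357 − 1.960) = 83.8% (81.9% with 38 practice-level degrees of freedom). The stated >80% is reproduced for a single comparison at 12 months.

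**2. What the stated model estimates.** With complete data and baseline, 6 and 12 months as responses, the treatment coefficient is (d0 + d6 + d12)/3, with d0 = 0 in expectation under randomisation. For d12 = 4:
- full effect by 6 months: (0 + 4 + 4)/3 = 2.67
- linear growth: (0 + 2 + 4)/3 = 2.00

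This needs no assumption about ρ. With 12 patients per practice at baseline and 10 at month 12, exact generalised least squares gives slightly less, about 2.56 and 1.84.

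**3. Power of that test.** The variance of the arm difference is (2/20) × [σp² + σs²/10 + σe²/30], where σp² = 0.01 × 169 = 1.69, σs² = (ρ − 0.01) × 169 and σe² = (1 − ρ) × 169.
- ρ = 0.5: 0.1 × (1.69 + 8.281 + 2.817) = 1.279, SE 1.131
- ρ = 0.8: 0.1 × (1.69 + 13.351 + 1.127) = 1.617, SE 1.272

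| Course of effect | Estimate | Power, ρ = 0.5 | Power, ρ = 0.8 |
|---|---|---|---|
| Full by 6 months | 2.67 | 65% | 55% |
| Linear growth | 2.00 | 42% | 35% |
| 12-month comparison alone (step 1) | 4.00 | 83.8% | 83.8% |

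**4. If only 6 and 12 months are responses.** The coefficient is (d6 + d12)/2: 4.0 if the effect is constant, 3.0 if it grows linearly. Replacing σe²/30 by σe²/20 gives SE 1.191 (ρ = 0.5) and 1.293 (ρ = 0.8). Power is then 92% to 87% for a constant effect and 71% to 64% for linear growth. The dilution is milder, but the target is still not the 12-month difference unless d6 = d12.

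**5. With an arm-by-visit term and a 12-month contrast.** The estimate is the full 4.0, with SE 1.357 and power 83.8%, as in step 1. Adding baseline as a covariate gives a residual SD of 13 × √(1 − ρ²): 11.26 (ρ = 0.5) or 7.80 (ρ = 0.8). Keeping the 1.09 design effect, SE = SD × √(2 × 1.09/200) = 1.175 or 0.814, and power is 92.6% or 99.8%.

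**The case against.** The strongest defence is that the dilution rests on two readings the text does not state. The sentence lists the factors of an analysis of variance without excluding their interaction, and condensed articles often leave the crossing unsaid. Nor does it say that baseline is a response. The 12-month outcome in the abstract suggests that the authors wanted a contrast at that visit, and a full factorial model would supply it. That much stands: a reader might infer that the plan rules out an interaction, and it does not. But the article does choose to fix the model that estimates and tests the effect. On the kinder readings the 12-month contrast is still unnamed, which leaves a main effect, an overall interaction test or a single contrast open as the primary test.

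Three stronger readings are tempting and should not be drawn.

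- *Adding an interaction would leave standard errors badly too small.* With only practice and patient intercepts, practice does cancel from a change-from-baseline test, and practice-level variation in change is then ignored. Serious inflation of that test, however, needs practice-by-time variance well above the protocol's ICC of 0.01. At that ICC, the type I error of the 12-month contrast stays near 5–6% (5.0% to 5.3% in simulation with ρ = 0.7).
- *Leaving out baseline SGRQ is an error.* It is not. The unadjusted 12-month comparison already has the planned power.
- *The sample size is wrong.* For this outcome the stated power reproduces. The mismatch lies in the model.

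**Conclusion.** The point holds: the model as stated does not deliver the 12-month difference that defines the primary outcome. Followed literally with baseline as a response, it shrinks a true 4-point effect by one third (full by 6 months) or one half (linear growth), and power falls from 83.8% to about 55–65% or 35–42%. The shrinkage depends only on the 6-month effect. The power figures also depend on the assumed correlation of 0.5–0.8. Both depend on taking the list of fixed effects as complete and baseline as a response, which is inferred from Table 1 and the visit schedule. If only follow-up visits are responses, the loss is smaller, and it disappears for a constant effect. If an interaction was intended and the 12-month contrast is the test, there is no loss, but the text has to say so.

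**What to change.** - Name the arm difference in SGRQ at 12 months as the primary estimate and the primary test.
- Fit the 6- and 12-month scores with baseline SGRQ as a covariate, fixed effects for visit, arm and arm-by-visit, and random effects for practice and patient. A 12-month analysis of covariance with a practice random intercept is a simpler alternative.
- State the analogous 12-month contrast for the other continuous outcomes and for the dichotomous ones.
- A practice-by-visit random effect may be added as an optional safeguard.

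The cost is a few sentences in the Data analysis section. All the SGRQ data needed are already scheduled, and the sample size does not change. Baseline adjustment comes free and would raise power to about 93% or more under the assumptions above.

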### Study design

This pragmatic cluster randomized controlled trial will test the hypothesis that early intervention by a practice nurse-GP partnership will improve outcomes for patients newly diagnosed with COPD, compared with usual care. Because the intervention involves a team approach by treating practitioners, randomization will occur at the practice level rather than at the level of individual patients (CONSORT guidelines for cluster trials [38,39]). All participating practices will use case-finding methods to identify a cohort of patients with newly diagnosed COPD.

The research plan, identifying recruitment strategies, randomization, data collection points, and the relationships between intervention and control groups in the two arms are summarised in Figure 1. Because it is a complex intervention with potential for variable implementation, there will be a focus on process evaluation as well as quantitative outcome measures.

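### The SGRQ mixed model names no 12-month contrast, and if that effect is tested as arm-by-visit its two random intercepts give no protection against practices changing differently over the year

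*Protocol article*

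**What the plan says.** The Data analysis section of the protocol article specifies, for continuous outcomes such as SGRQ, a "mixed model analysis of variance in which time and treatment group will be fixed effects", and adds that "GP practice and subject nested within practice will be random effects". It names no group-by-time interaction, no practice-by-time effect and no contrast.

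Table 1 lists SGRQ at visits 1, 2 and 3 (baseline, 6 and 12 months), so baseline is one of the repeated measurements. The Design paragraph of the abstract defines the primary outcome as health-related quality of life "assessed with the St George’s Respiratory Questionnaire 12 months after diagnosis".

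Under Study design, "randomization will occur at the practice level rather than at the level of individual patients". The Sample size calculations section uses an "intra-cluster correlation coefficient of 0.01, and a resultant design effect of 1.09 for a cluster size of 10".

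**The concern.** A treatment main effect in this model averages the arms over all three visits, including the one before any intervention. That is not the 12-month effect made primary in the abstract. The usual way to obtain a 12-month effect from a repeated-measures model that includes baseline is an arm-by-visit term, read as the difference between arms in change from baseline.

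Both stated random effects are intercepts, constant over visits. In a change from baseline they subtract out, so the contrast is judged against patient-by-visit residual error, much as if patients had been individually randomised. Practices may well differ in how their patients change over the year: the Study design section itself expects delivery of this complex intervention to vary. That variation would then be missing from the standard error. The sample size would carry a design effect of 1.09 while the primary test carried about 1. Intervals would be too narrow and the false-positive rate above 5%.

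**Working it through.** **Plan's own figure.** Design effect = 1 + (10 − 1) × 0.01 = 1.09. Effective size per arm = 200/1.09 = 183.5. With a difference of 4 and SD 13, 4 / (13 × √(2/183.5)) = 2.947, and power = Φ(2.947 − 1.96) = 83.8%. The stated power of more than 80% is reproduced. Two-sided 5% is assumed, because the article states 5% only for inhaler use.

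**Inputs from the article.** 40 practices (taken as 20 per arm), m = 10 patients per practice, n = 200 per arm, T = 3 visits, total variance V = 13² = 169, ICC ρ = 0.01.

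**Assumptions not in the article.** Within-patient correlation r = 0.7; share s of practice variance that is visit-specific, from 0 to 1; ICC 0.05 as a sensitivity value; complete data.

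**Change contrast (baseline to 12 months, arm difference).**
- Practice-by-visit variance: P = Vρs
- Residual variance: E = V(1 − r) − P = 50.7 − P
- True variance of the contrast: 4 × (E/200 + P/20)
- Variance the model reports: 4 × M/200, where M = E + 10P × 38/398 is the expected residual mean square when practice-by-visit variation is pooled into it
- Type I error: 2 × [1 − Φ(1.96 × model SE / true SE)]

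Example, ρ = 0.01 and s = 0.5:
- P = 0.845 and E = 49.855.
- True variance = 4 × (0.2493 + 0.0423) = 1.166, SE 1.080.
- M = 49.855 + 0.807 = 50.662, so model variance = 1.013, SE 1.007.
- Ratio 0.932, type I error 6.8%.
- The design effect needed for this contrast is 1 + 9 × (0.845/50.7) = 1.15. The model supplies about 1.

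| ICC | share visit-specific | model SE | true SE | type I error | simulated |
|---|---|---|---|---|---|
| 0.01 | 0 | 1.007 | 1.007 | 5.0% | 4.8% |
| 0.01 | 0.2 | 1.007 | 1.037 | 5.7% | 5.4% |
| 0.01 | 0.5 | 1.007 | 1.080 | 6.8% | 6.5% |
| 0.01 | 1 | 1.006 | 1.148 | 8.6% | 8.1% |
| 0.05 | 0.2 | 1.006 | 1.148 | 8.6% | 8.1% |
| 0.05 | 0.5 | 1.005 | 1.332 | 13.9% | 14.0% |

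Simulations used 4,000 null trials per setting. Testing practice-mean changes on 38 df gave 4.6% to 5.1% in the same settings.

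**Plain arm difference at 12 months, from a model with arm-by-visit means and the same random part.** Here the practice intercept does not cancel. With stable practice variance S = Vρ(1 − s) and patient variance B = Vr − S:
- True variance: 2 × (E + B + 10S + 10P)/200
- Model variance: 2 × (E/3 + 10P/3 + B + 10S + 2M/3)/200

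At ρ = 0.01 the model-to-true SE ratio is 1.000, 0.994, 0.986 and 0.972 for s = 0, 0.2, 0.5 and 1, giving type I error of 5.0% to 5.7%. Simulation gave 4.3% to 5.1%, using t on 38 df and pooling when the practice variance estimate was negative. At ρ = 0.05 and s = 0.5 the SEs are 1.482 and 1.565, and type I error is 6.3% to 6.4%.

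**Group main effect over visits (the fixed effects as literally written).** The practice intercept stays in the standard error; simulated type I error was 3.8% to 5.2% at ICC 0.01 and 0.05.

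**The case against.** The strongest reply is that the article never states the contrast at issue. It names no interaction and no change score. The abstract describes SGRQ at 12 months, and the sample size is built on a between-subject SD of 13, not the SD of a change. All of this fits a plain arm difference at 12 months, for which the stated random part is adequate at the planned ICC. The plan also includes practice as a random effect, inflates for clustering and promises to publish ICCs. This reply stands, and it makes the finding conditional. It does not settle the matter, because the text leaves the choice open and one ordinary choice loses the protection.

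A reader might infer that the primary standard errors are certainly too small and the false-positive rate certainly above 5%. The article does not support that. It requires both an arm-by-visit test and practice variance that shifts between visits. With fully stable practice variance the change contrast also runs at 5%.

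A reader might also add the effect of a single patient intercept, which forces equal correlation between all pairs of visits. If correlation were 0.8 six months apart and 0.7 twelve months apart, the variance of a 12-month change would be understated by (1 − 0.7)/(1 − 0.767) = 1.286, giving 8.4% by itself. Those correlations are assumed, the article states no residual covariance, and the same problem would arise without clusters. It supports freeing the covariance as part of the fix but is not evidence about clustering.

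**Conclusion.** The point holds in conditional form. The model does not fix the contrast for the 12-month effect, and its random part cannot protect an arm-by-visit test.

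At the plan's own ICC the excess is modest: up to 3.6 percentage points over 5%, and that maximum needs all practice variance to be visit-specific. Inflation to nearly 14% needs an ICC five times the planning value with half of it visit-specific. These sizes rest on the assumed correlation of 0.7, the assumed visit-specific shares and complete data; with dropout the intercepts cancel only approximately.

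Severity is moderate. It concerns the primary test of a practice-randomised trial and is easily closed, but the figures at ICC 0.01 do not make it a must-fix.

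**What to change.** In the Data analysis section, name the arm contrast in SGRQ at 12 months as the primary effect, and say whether it is a difference at 12 months or a difference in change from baseline. Then take one of two routes:

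- **If it comes from an arm-by-visit term:** add a random practice-by-visit effect, allow an unstructured within-patient covariance over the three visits, and test on practice-level degrees of freedom (40 − 2 = 38). Keep the 38 even if the practice-by-visit variance is estimated at zero.
- **Alternatively:** analyse 12-month SGRQ adjusted for baseline SGRQ, with a practice random effect and the same degrees of freedom.

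Apply the same choice to the other continuous outcomes, since the section gives them the same model. The cost is a sentence or two of text and slightly wider intervals. On the plan's own inputs, moving from a normal reference to t on 38 df takes power from 83.8% to 81.9%, still above 80%. No extra data are needed.
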